## Abstract

**Methods::**

This is a 2-arm, feasibility cluster RCT with a blinded outcome assessment and a qualitative evaluation. The study is conducted in 12 public and private ayurveda centers in and outside the Kathmandu Valley in Nepal (1:1 intervention:control). Eligible participants should be new T2DM adult patients (i.e., treatment naïve) - the glycated hemoglobin level should be 6.5% or above but less than 9%. At least 120 participants (60/group) will be recruited and followed up for 6 months. Important parameters, needed to design the definitive trial, will be estimated, such as the standard deviation of the outcome measure (i.e., glycated hemoglobin level at 6-month follow-up), intraclass correlation coefficient, cluster size, recruitment, the time needed to recruit participants, follow-up, and adherence to the recommended ayurvedic medicine. Semi-structured qualitative interviews will be conducted with around 20 to 30 participants and all the participating ayurvedic practitioners to explore their experiences and perspectives of taking part in the study and of the intervention and a sample of eligible people declining to participate in the study to explore the reasons behind nonparticipation.

**Discussion::**

We are now conducting a feasibility cluster RCT in Nepal to determine the feasibility of undertaking the definitive cluster trial. The first participant was recruited on 17 July 2022. If the feasibility is promising (such as recruitment, follow-up, and adherence to the recommended ayurvedic medicine), then the parameters estimated will be used to design the definitive cluster trial. Decisions over whether to modify the protocol will mainly be informed by the qualitative data.

## 1. Introduction

Diabetes mellitus is one of the most common chronic diseases, and its global prevalence is increasing.^[1]^ Currently, 1 in 10 adults is living with diabetes, and around 44% are undiagnosed.^[1]^ About 90% of adults currently diagnosed have type 2 diabetes its global prevalence is increasing.[1] Currently, 1 in 10 adults is currently undiagnosed.^[1]^ T2DM is a complex metabolic disorder with significant health and socioeconomic consequences.^[1,2]^ Chronic hyperglycemia in T2DM is associated with macrovascular and microvascular complications and even death.^[1,2]^ In Nepal, the prevalence of T2DM between 2010 and 2015 was around 8% (95% confidence interval (CI): 4–16), which increased to 11% (8–16) between 2015 and 2020.^[3]^

In Nepal, ayurveda is a dominant traditional medical system and has been in use for thousands of years.^[4]^ Qualified and registered ayurvedic practitioners are employed in the public and private healthcare system (e.g., in ayurveda centers), often as the main clinical provider.^[5]^ The corresponding term for diabetes mellitus in ayurveda is madhumeha (madhu means “sweetness” and meha means “excessive urination”).^[6,7]^ The condition and its management have been described in detail in classical ayurvedic texts.^[6,7]^ Briefly, a multipronged approach is used to manage the condition, such as through lifestyle changes and ayurvedic medicines (containing plant-, animal-, or mineral-origin ingredients–single or in combination). It is hypothesized that many of these ayurvedic medicines work through pancreatic and extrapancreatic effects.^[6,7]^ T2DM is one of the common diseases for which patients consult ayurvedic practitioners, and many people with T2DM use ayurvedic medicines, often continuously from the point of diagnosis.^[5,8]^ Ayurveda fits their health beliefs and culture, and acceptability, satisfaction, and perceived relief are usually high, especially among rural, poor, older, and tribal populations.^[8–10]^ Many people with T2DM prefer not to use western medicines in order to avoid their side effects, cost, and mode of administration like insulin injections.^[8,9,11,12]^

Strong concerns remain about the suboptimal T2DM management of many patients by ayurvedic practitioners, and the actions to be taken at different stages of the T2DM care pathway are largely left to the judgment of the individual ayurvedic practitioner (including screening for complications and referral to specialist services for complications management), resulting in unacceptable variations in ayurvedic clinical practice.^[13–15]^ Many nonevidence-based ayurvedic medicines are prescribed by them, which can have serious adverse effects on patients, including heavy metal poisoning.^[16]^ Many times ayurvedic practitioners blindly follow the claims made by others or opt for a “trial and error” approach.^[15,17]^ One of the main barriers highlighted by ayurvedic practitioners is the absence of a good quality clinical guideline to deliver quality care to people with T2DM.^[15]^

In western medicine, clinical guidelines have been used to improve the clinical care of people with T2DM.^[18,19]^ However, no such clinical guideline for managing T2DM is available in Nepal for ayurvedic practitioners. A good quality clinical guideline, based on the best available scientific evidence, to manage T2DM by ayurvedic practitioners may address the existing problems and deter the usage of ayurvedic medicines of no, minimal, or questionable value and promote the usage of effective and safe ayurvedic medicines. It will aid their clinical decision-making process through recommended actions at various stages of the T2DM care pathway. It may close the gap between what they do to manage T2DM and what the scientific evidence supports.

The introduction of a clinical guideline is not always effective in improving the outcomes (including patients’ health), and it needs to be evaluated in the target population and healthcare setting before scaling up.^[20–22]^ This is particularly important in this case where an innovative approach is used to integrate ayurvedic and western medical systems. Therefore, the principal research question to be addressed by a definitive cluster randomized controlled trial (RCT) is whether the introduction of a clinical guideline can improve the management of T2DM by ayurvedic practitioners in Nepal as compared to usual ayurvedic management. In preparation for this future work, this current study aims to determine the feasibility of undertaking the definitive cluster RCT. The chances of successful completion of a costly definitive trial improve if the feasibility of its key elements is checked before it starts, and important parameters, needed to design the definitive trial, are estimated.^[23]^

## 2. Methods

### 2.1. Study design

This is a 2-arm, feasibility cluster RCT with a blinded outcome assessment and a qualitative evaluation.

### 2.2. Study setting

The study is conducted in 12 public and private ayurveda centers (clusters) in and outside the Kathmandu Valley in Nepal. These centers have a minimum of one ayurvedic practitioner with at least 5½ years of an undergraduate medical degree in ayurveda. All the centers approached are participating in the study. People from a wide range of socioeconomic backgrounds access these centers.

### 2.3. Randomization and blinding

Ayurveda centers are randomized to the intervention or control group according to a computer-generated randomization schedule (1:1 using Random Allocation Software Version 1.0), performed by an independent statistician at the Nepal Health Research Council, Kathmandu, Nepal. Ayurvedic practitioners and participants cannot be “blinded” to group allocation, but the outcome assessors are “blind”. The outcome assessors are an independent team of trained researchers. To give some protection against contamination, intervention group ayurvedic practitioners have signed a nondisclosure form, and they are not allowed to disclose the content of the intervention to anyone.

### 2.4. Intervention

In the intervention group, ayurvedic practitioners will manage T2DM based on a clinical guideline developed by us. The intervention development process will be published elsewhere, and the clinical guideline is based on the best available scientific evidence. Briefly, a systematic process was followed to develop the clinical guideline, guided by the Grading of Recommendations, Assessment, Development and Evaluation (GRADE) approach, the UK’s National Institute for Health and Care Excellence manual for developing guidelines, and the Appraisal of Guidelines for Research and Evaluation (AGREE) II instrument.^[24–26]^ Initially, we conducted a comprehensive systematic review assessing the effectiveness and safety of ayurvedic medicines for managing T2DM and the certainty of the findings using the GRADE approach.^[27]^ Subsequently, based on the GRADE approach, we developed the Evidence-to-Decision framework, focusing on glycemic control and adverse events. Based on the Evidence-to-Decision framework, a Guideline Development Group, comprising 17 international members, made recommendations on the effectiveness and safety of ayurvedic medicines in T2DM. The recommendations formed the basis of a clinical guideline, with further generic content and recommendations adapted from the T2DM Clinical Knowledge Summaries of the Clarity Informatics (UK).^[28]^ The Guideline Development Group gave feedback on the draft version, which was used to amend and finalize the clinical guideline. The clinical guideline will support ayurvedic practitioners in providing appropriate care, education, and support to participants (and their carers and family). The clinical guideline covers topics like diagnosis, management through lifestyle advice and ayurvedic medicines, screening for complications, and referral to specialist services for complications management. Regular training is provided to ayurvedic practitioners in the use of the clinical guideline which involves roleplaying and structured and instructive feedback to improve their performance. To maximize the implementation of the clinical guideline, a prescription pad based on the clinical guideline is provided to the ayurvedic practitioners to help them to provide relevant advice to the participants, and an ayurvedic medicine recommended in the clinical guideline is provided free of cost to the participants for the duration of the study.

### 2.5. Control

No clinical guideline is available in Nepal to manage T2DM by ayurvedic practitioners. Thus, the comparator will be the usual management of T2DM (i.e., without any clinical guideline) by ayurvedic practitioners.

### 2.6. Eligibility criteria

#### 2.6.1. Inclusion criteria

Participants should be:

Adults (aged ≥ 18 years).New T2DM patients (i.e., treatment naïve to any blood glucose-lowering medication) - the glycated hemoglobin (HbA1c) level should be 6.5% or above^[28]^ but less than 9%.

#### 2.6.2. Exclusion criteria

Pregnant women.Those with any serious or uncontrolled medical condition (e.g., cancer).Those currently receiving (or with plans to receive during the study period) any related non-pharmaceutical or pharmaceutical research intervention.

### 2.7. Screening, recruitment, and follow-up

Adults visiting the ayurveda centers with possible clinical features of T2DM and/or hyperglycemia (i.e., HbA1c of 6.5–9%, fasting blood glucose of ≥ 126 mg/dL, or random blood glucose ≥ 200 mg/dL) but treatment naïve are approached for screening. The participant information sheet is given to these potential participants, including a verbal description of the study and answering their questions. Those interested in the study are requested to provide written informed consent. The participant information sheet and consent form are available in Nepali and English. Those providing written informed consent are assessed against the study eligibility criteria, and their HbA1c is determined using a venous blood sample (see Table 1). After the recruitment of a participant, baseline data are collected by “blind” outcome assessors. Each participant will be followed up for 6 months.

**Table 1 T1:** Data collection.

		Face-to-face assessments		
	Assessment details	Screening and recruitment	Baseline	Final at 6-mo follow-up (±5 d)
Eligibility assessment		√		
Sociodemographics	Patient reported		√	
Medical and surgical history	Patient reported		√	
Family history of diabetes	Patient reported		√	
Current concomitant medications (any medical system)	Patient reported		√	√
Biochemical parameters				
*Blood glucose*				
Glycated hemoglobin*	High-performance liquid chromatography (HPLC) method	√		√
Fasting blood glucose†	Glucose oxidase-peroxidase (GOD-POD) method		√	√
*Lipid profile*				
Total cholesterol	Cholesterol oxidase method		√	√
High-density lipoprotein	Direct clearance method		√	√
Low-density lipoprotein	Direct clearance method		√	√
Very low-density lipoprotein	Calculated value		√	√
Triglyceride	Lipase/glycerol-3-phosphate oxidase-phenol + aminophenazone (GPO-PAP) no correction method		√	√
*Liver function tests*				
Albumin	Spectrophotometry (Bromocresol green method)		√	√
Total bilirubin	Spectrophotometry (modified Jendrassik and Grof method)		√	√
Direct bilirubin	Spectrophotometry (modified Jendrassik and Grof method)		√	√
Indirect bilirubin	Spectrophotometry (modified Jendrassik and Grof method)		√	√
Alkaline phosphatase	Ultraviolet (UV) kinetic (modified IFCC method)		√	√
Alanine transaminase (ALT)	UV kinetic (modified IFCC method)		√	√
Aspartate transaminase (AST)	UV kinetic (modified International Federation of Clinical Chemistry and Laboratory Medicine (IFCC) method)		√	√
AST-ALT ratio	Calculated value		√	√
*Electrolytes*				
Sodium	Ion selective electrode (ISE)		√	√
Potassium	ISE		√	√
Urea	Spectrophotometry (Berthelot method)		√	√
Creatinine	Spectrophotometry (modified Jaffe’s method)		√	√
*Urine albumin-to-creatinine ratio*	Spectrophotometry		√	√
Physiological parameters†				
Blood pressure	Omron HEM-8712		√	√
Heart rate	Omron HEM-8712		√	√
Anthropometric parameters†				
Waist circumference	Seca 201 (measuring tape)		√	√
Bodyweight	[name] (weighing scale)		√	√
Height	Stature meter		√	√
Body mass index	Calculated value		√	√
Lifestyle				
Diet	Patient reported		√	√
Physical activity	Patient reported International Physical Activity Questionnaire (IPAQ)–Short^[29]^		√	√
Tobacco usage	Patient reported		√	√
Alcohol consumption	Patient reported		√	√
Health-related quality-of-life	Patient reported EuroQol-5D-5L (EQ-5D-5L)^[30]^		√	√
Depression, anxiety, and stress	Patient reported Depression, Anxiety and Stress Scale (DASS-21)^[31]^		√	√
Perception of illness	Patient reported Brief Illness Perception Questionnaire (BIPQ)^[32]^		√	√
Satisfaction with treatment	Patient reported Short Assessment of Patient Satisfaction (SAPS)^[33]^			√

* Also assessed at 3-month follow-up.

† Also assessed at 1-month follow-up.

### 2.8. Study parameters and data collection

#### 2.8.1. Cluster RCT

For sample size calculation of the definitive cluster RCT:The standard deviation (SD) of the primary outcome measure (i.e., HbA1c level at 6-month follow-up).Another estimate of intraclass correlation coefficient and cluster size (i.e., the number of participants recruited per ayurveda center during the recruitment period).Recruitment: The number of people approached to participate, written informed consent given, screened for eligibility, found eligible, and recruited.The time needed to recruit participants.Follow-up: The number of participants followed up for 6 months.Adherence: In the intervention group, the number of participants adhering to the recommended ayurvedic medicine (assessed using a self-reported diary and by medicine counting at the sites).Others: See Table 1.

A standard operating procedure is developed and used for data collection. Blood and urine samples are collected and analyzed at local laboratories, accredited by the National Public Health Laboratory in Nepal.

### 2.8.2. Qualitative evaluation

Interviews will be conducted with participants to explore their experiences and perspectives of taking part in the study (intervention and control group participants who complete or do not complete the study) and of the intervention (intervention group only).Eligible people who decline to participate in the study will be requested to complete a questionnaire (including reasons behind nonparticipation). A sample of these people (who agree to be interviewed) will be interviewed to further explore their reasons for nonparticipation.Interviews will be conducted with all the participating ayurvedic practitioners to explore their experiences and perspectives of taking part in the study (both the groups) and of the intervention (intervention group only and focusing on topics like its acceptability and factors that facilitated or impeded its uptake and adherence).

Predeveloped interview guides will be used by a qualitative researcher to conduct these semi-structured interviews. The interviews will be conducted in the interviewees’ preferred language and with the help of an interpreter if needed. With consent, these will be noted and digitally recorded.

### 2.9. Data analyses

#### 2.9.1. Cluster RCT.

We will summarize the data using numbers and percentages for categorical data and summary measures of mean or median and spread for continuous data. Being a feasibility cluster RCT, it is not adequately powered to detect a difference in trial outcomes between the 2 arms. However, unadjusted mean difference or odds ratio with 95% CI will be reported to indicate initial estimates of effects. Subsequently, for critical outcomes like HbA1c, ANCOVA analysis will be conducted, allowing for clustering and adjustments made for the individual’s baseline value and subsequently, also for the individual’s age and sex and cluster (ayurveda center) mean.^[34]^ The regression coefficient and 95% CI will be reported. All analyses will be based on the intention-to-treat principle. Being a short-term feasibility study, no interim analysis is planned. STATA V.17 will be used for data analyses.

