### 2.10. Sample size

#### 2.10.1. Cluster RCT.

A formal sample size calculation is not usually required for a feasibility trial, and it is recommended to recruit at least 50 participants in a feasibility trial.^[36]^ After taking into account the cluster study design and loss to follow-up, we will recruit at least 120 participants (60/group) in this feasibility cluster RCT to estimate the SD of the primary outcome measure (i.e., HbA1c level at 6-month follow-up). This sample size is calculated in relation to the desired level of confidence (95%) for the SD, the chosen power (80%) and significance level (5%, 2-tailed), and the expected loss to follow-up (20% at 6 months), intraclass correlation coefficient (0.03), and mean cluster size (10 participants).^[36–38]^

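### Clustering is allowed for only in the later ANCOVA of critical outcomes, so on the natural reading the unadjusted 95% CIs, including all odds ratios, treat participants as independent

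*Protocol article*

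**What the plan says.** The design is clustered. Section 2.2 states: "The study is conducted in 12 public and private ayurveda centers (clusters) in and outside the Kathmandu Valley in Nepal". Section 2.3 states: "Ayurveda centers are randomized to the intervention or control group according to a computer-generated randomization schedule", in a 1:1 ratio, which gives 6 centres per arm.

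The sample size section (2.10.1) recognises the clustering. It lists an "intraclass correlation coefficient (0.03), and mean cluster size (10 participants") among its inputs, together with 20% loss to follow-up at 6 months. Section 2.8.1 makes the intraclass correlation one of the quantities to be estimated.

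The analysis section (2.9.1) has two steps for comparing the arms:

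- Step one: an "unadjusted mean difference or odds ratio with 95% CI will be reported to indicate initial estimates of effects". Nothing is said about centres.
- Step two, introduced as subsequent: "for critical outcomes like HbA1c, ANCOVA analysis will be conducted, allowing for clustering and adjustments made for the" participant's own baseline value, and then also for age, sex and the centre mean.

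The critical outcomes are not listed beyond the example of HbA1c.

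**The concern.** The words about clustering belong to step two alone, and step two is limited to critical outcomes and to ANCOVA, a method for continuous outcomes. Read in the ordinary way, the step-one intervals are participant-level. For any odds ratio, and for any continuous outcome not treated as critical, that would be the only between-arm interval reported.

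Participants from the same centre share a practitioner and a setting, and the plan itself assumes that their outcomes are correlated. An interval that ignores this is too narrow for a comparison of 6 centres with 6. In a trial that is openly not powered to detect a difference, the interval is the main statement of how uncertain the effect is. Table 1 lists some 34 parameters at 6 months, so intervals that are too narrow could suggest differences that the design does not support.

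**Working it through.** **Inputs from the documents.** 12 centres, 6 per arm (2.2, 2.3); "we will recruit at least 120 participants (60/group) in this feasibility cluster RCT"; intraclass correlation (ICC) 0.03, mean cluster size 10 and 20% loss (2.10.1). After loss, 10 × 0.8 = 8 participants per centre, or 96 in total.

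**The plan's own figure.** 12 × 10 = 120 agrees with the stated total. The section also says that "it is recommended to recruit at least 50 participants in a feasibility trial". Starting from 50, the design effect and loss give 50 × 1.27 / 0.8 = 79.4, so 80, not 120. The section does not give the base number behind the confidence and power that it names, so 120 can be neither reproduced nor called wrong. The present point does not depend on it.

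**Design effect.** 1 + (m − 1) × ICC:

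- m = 8: 1 + 7 × 0.03 = 1.21, so true SE / participant-level SE = √1.21 = 1.10
- m = 10: 1 + 9 × 0.03 = 1.27, so the ratio is √1.27 = 1.13

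**Coverage of the participant-level 95% interval, normal approximation.** 2Φ(t / √design effect) − 1, with t on N − 2 degrees of freedom:

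- m = 8 (N = 96, t = 1.986): 1.986 / 1.10 = 1.805, coverage 92.9%
- m = 10 (N = 120, t = 1.980): 1.980 / 1.127 = 1.757, coverage 92.1%

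**Simulation.** 40,000 trials per setting, equal centre sizes, continuous outcome, no true effect. Only the ICC of 0.03 comes from the plan; the other values are assumptions that show the range.

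| ICC | Coverage, 8 per centre | Coverage, 10 per centre |
|---|---|---|
| 0.01 (assumed) | 94.2% | 94.0% |
| 0.03 (plan) | 92.7% | 91.8% |
| 0.05 (assumed) | 90.8% | 89.6% |
| 0.10 (assumed) | 86.7% | 84.4% |

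A t interval on centre means with 12 − 2 = 10 degrees of freedom covered 94.8 to 95.1% in the same simulations.

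**Width after correction at ICC 0.03.** The two sources multiply, with t on 10 degrees of freedom = 2.228:

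- m = 8: 1.10 (clustering) × 2.228 / 1.986 = 1.10 × 1.122 = 1.23. The half-width goes from 0.405 to 0.500 SD.
- m = 10: 1.127 × 2.228 / 1.980 = 1.127 × 1.125 = 1.27. The half-width goes from 0.362 to 0.458 SD.

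Ignoring the centre thus accounts for 10 to 13% of extra width. The remainder comes from the small number of clusters.

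**The case against.** The strongest reply is that *unadjusted* may mean only unadjusted for covariates. The article nowhere states that these intervals ignore the centre, so a reader who takes that as an express statement goes too far. This stands as a limit on certainty. Still, clustering is named solely as a feature of the later step, so the participant-level reading is the more natural one. The reply that such matters are left to an analysis plan does not dispose of the point, because the article does address clustering and attaches it to a subset of the analyses.

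Three stronger readings are tempting, and the documents do not support them:

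- *Most outcomes get only an unclustered interval.* The critical outcomes form an open list, so their share cannot be established. HbA1c, the primary outcome, does get a clustered interval.
- *The clustered ANCOVA will itself be too narrow because it uses z or participant-level degrees of freedom.* The article names no such choice. That detail is commonly left to the analysis plan and is not an error here.
- *The intervals will steer the definitive trial.* Section 2.8.1 and the Discussion name the SD, intraclass correlation, cluster size, recruitment, follow-up and adherence for that purpose, and rest protocol changes mainly on the qualitative data. No passage gives the effect intervals a part in that decision.

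It is also fair to say that the estimates are labelled initial, in a study declared not adequately powered. This limits the consequence but does not make the intervals correct.

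**Conclusion.** The point holds on the natural reading of section 2.9.1. Unadjusted intervals calculated as written would understate the uncertainty in a trial that randomised 12 centres. At the plan's own intraclass correlation the shortfall is modest: a true standard error 10 to 13% larger, and coverage of about 92% in place of 95%. It would be worse if outcomes cluster more strongly, at about 90% coverage for 0.05 and 84–87% for 0.10, but those values are assumptions. It would be slight at 0.01.

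The figures assume equal centre sizes and a continuous outcome; odds ratios were not simulated. With the clustered HbA1c analysis in place and no decision tied to these intervals, this is a moderate matter that should be fixed before analysis. It does not threaten the aims of the study.

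**What to change.** In section 2.9.1, state that every between-arm estimate and 95% CI, including those unadjusted for covariates, allows for centre by a method suited to 12 clusters. Suitable choices are:

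- for continuous outcomes, a t analysis of centre means on 10 degrees of freedom, or a mixed model with a centre random effect and small-sample degrees of freedom (Kenward-Roger or Satterthwaite);
- for odds ratios, GEE with a small-sample correction.

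List the critical outcomes in the same place. If the unadjusted intervals were always meant to allow for centre, saying so settles the point.

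The cost is one or two sentences and different software options, with no change to design or data collection. At an intraclass correlation of 0.03 the reported intervals for continuous outcomes become about 23 to 27% wider than participant-level ones.

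### Baseline adjustment is limited to an open-ended set of critical outcomes, so any other continuous outcome gets only a raw 6-month difference although its baseline value is collected

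*Protocol article*

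**What the plan says.** Section 2.9.1 sets out two steps. First, an "unadjusted mean difference or odds ratio with 95% CI will be reported to indicate initial estimates of effects". Second, "for critical outcomes like HbA1c, ANCOVA analysis will be conducted, allowing for clustering and adjustments made for the individual’s baseline value", with age, sex and the center mean added in a further model. Allowance for clustering is mentioned only in the second step. The same section states of the trial that "it is not adequately powered to detect a difference in trial outcomes between the 2 arms".

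Table 1 (section 2.7) ticks both baseline and 6 months for fasting glucose, lipids, liver and kidney tests, blood pressure, weight, BMI, waist, physical activity, EQ-5D-5L, DASS-21 and illness perception. HbA1c is taken at screening and at follow-up. Of the outcome scales, only treatment satisfaction has no baseline value. The text of section 2.7 adds: "After the recruitment of a participant, baseline data are collected by “blind” outcome assessors".

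On allocation, section 2.3 says: "Ayurveda centers are randomized to the intervention or control group according to a computer-generated randomization schedule". The ratio is 1:1 across 12 centers. No stratification or matching is described, and practitioners and participants know their group.

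**The concern.** The plan collects a baseline value for almost every continuous outcome and names a suitable model that uses it, but confines that model to a subset it does not define. For a continuous outcome outside that subset, the reported effect is the raw difference in 6-month means. Two things follow.

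- **Point estimate.** Six centers per arm, randomized without described stratification, will differ at baseline by chance. Because practitioners are unblinded, recruitment may also differ between arms. A raw 6-month difference passes on part of any such imbalance, and a reader of the results could take it for benefit or harm.
- **Precision.** Variation that the baseline value explains stays in the error term, although the data to remove it are already in hand.

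At stake is the quality of the secondary effect estimates that the investigators choose to publish with 95% confidence intervals. The primary outcome is not affected, because HbA1c is named as adjusted.

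**Working it through.** The protocol gives no figure for interval width or baseline imbalance, so there is nothing of its own to reproduce on this point.

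**Inputs from the protocol article**
- 12 centers, 1:1, so 6 per arm (sections 2.2 and 2.3).
- At least 120 participants, 60 per arm; 20% loss at 6 months; ICC 0.03; mean cluster size 10 (section 2.10.1).

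**Assumptions**
- Loss is even: 120 × 0.8 / 2 = 48 analyzed per arm, 8 per center.
- The ICC of 0.03 applies to the other continuous outcomes, at baseline and at 6 months.
- rho is not given. It is taken as 0.3, 0.5 or 0.7, equal within and between centers, with similar SDs at both times.
- Intervals use t on 12 − 2 = 10 degrees of freedom, with 97.5% point 2.228.

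**Design effect**, 1 + (m − 1) × ICC
- 8 per center: 1 + 7 × 0.03 = 1.21
- 10 per center: 1 + 9 × 0.03 = 1.27

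**Chance imbalance in a baseline mean**, in outcome SDs, sqrt(2 × DE / n per arm)
- All recruited: sqrt(2 × 1.27 / 60) = 0.206; 95% range ±1.96 × 0.206 = ±0.40
- Completers: sqrt(2 × 1.21 / 48) = 0.2245; 95% range ±1.96 × 0.2245 = ±0.44

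A raw 6-month difference carries about rho times the imbalance. For a one-SD imbalance (0.206 to 0.2245) that is 0.06 to 0.07 SD at rho 0.3, 0.10 to 0.11 SD at rho 0.5, and 0.14 to 0.16 SD at rho 0.7.

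**95% CI half-width, clustering allowed for in both analyses**, t × sqrt(2 × DE × (1 − rho²) / n)

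| rho | Half-width (SD) | Change from unadjusted |
|---|---|---|
| unadjusted | 2.228 × 0.2245 = 0.50 | – |
| 0.3 | 0.50 × sqrt(0.91) = 0.48 | 5% narrower |
| 0.5 | 0.50 × sqrt(0.75) = 0.43 | 13% narrower |
| 0.7 | 0.50 × sqrt(0.51) = 0.36 | 29% narrower |

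With no loss (60 per arm, design effect 1.27) the half-widths are 0.46 unadjusted and 0.44, 0.40 and 0.33 adjusted. The proportional gain is the same.

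**Where the width gain stops**
- *Clustering ignored in the unadjusted step.* The half-width is then t on 94 df × sqrt(2/48) = 0.405 SD. That is narrower than the clustered, adjusted interval at rho 0.3 (0.48) and 0.5 (0.43), and wider at 0.7 (0.36). The two are equal at rho of about 0.59.
- *Odds ratios.* In a simulation with 96 participants and an assumed log-odds slope of 1.2 per SD of baseline, the standard error of the log odds ratio rose from 0.41 unadjusted to 0.48 adjusted.

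**The case against.** The strongest reply is that the set is open. The phrase about critical outcomes is plural and illustrative, so weight, blood pressure or fasting glucose may belong to it, and a fuller analysis plan may list them. That stands: the number of outcomes left unadjusted is unknown, and the missing list is not the finding. What remains is the stated restriction itself, which a list would not lift for the outcomes left off it.

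Four stronger readings are tempting, and the document does not support them.

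- *A reader might infer that all the unadjusted intervals will be too wide.* The protocol mentions clustering only for the ANCOVA. If the unadjusted intervals ignore it, they may be too narrow instead. For odds ratios, adjustment does not shorten the interval.
- *A reader might infer that raw differences mostly show who enrolled at which center.* At the plan's ICC, the between-center part of the variance is 2 × 0.03 / 6 = 0.010 and the within-center part is 2 × 0.97 / 48 = 0.040, so about 80% is individual variation within centers. Chance imbalance also does not bias the unadjusted estimator, and a properly clustered interval already includes it.
- *A reader might infer that adjustment cures recruitment bias.* It removes only imbalance carried by the measured baseline value.
- *A reader might infer a loss of power, or a wrong choice for the definitive trial.* The plan disclaims power for effects. Section 3 ties going on to matters such as recruitment, follow-up and adherence, and says protocol changes will rest mainly on qualitative data. It links no decision to the secondary estimates.

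**Conclusion.** The point holds in a limited form. For any continuous outcome outside the critical set, the plan reports a raw 6-month difference and leaves a collected baseline value unused. The estimate then carries roughly rho times a baseline imbalance whose chance SD is about 0.21 to 0.22 outcome SDs. With clustering treated alike in both analyses, the half-width is about 0.50 SD where 0.48, 0.43 or 0.36 SD is available at rho 0.3, 0.5 or 0.7.

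These sizes rest on the plan's ICC holding for the other outcomes, on even loss across centers, and on an assumed rho. At rho 0.3 the gain in width is small. The point is not an error in the primary analysis and threatens no stated feasibility decision. It is an improvement worth making to exploratory secondary estimates, because it costs almost nothing.

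**What to change.** In section 2.9.1, extend the clustered, baseline-adjusted ANCOVA already specified for HbA1c to every continuous outcome measured at both baseline and 6 months, transforming skewed measures where needed. Report the adjusted result as the initial estimate of effect, with the unadjusted one beside it, and allow for clustering in both so that they can be compared. The further adjustment for age, sex and center mean can stay with the critical outcomes.

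The cost is a few more model fits and a simple stated rule for participants with a missing baseline value. No new data, visits or participants are needed.
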